###### Appendix C

Study Specific Questions

# Steps to Increase Physical Activity

# Study Specific Questions

## Adults (Males & Females) BMI **25 – < 35**

**Age 35-64 years**

### Design: 60 Volunteers (30 control group; 30 intervention group) for 3 weeks, 7 days each week.

#### YES NO

1. Do you have heart disease? ____ ____

2. Do you have diabetes? ____ ____

3. Do you have high blood pressure? ____ ____

If so, what medication are you on? **(Hytrin excludes) ____________________________**

4. Are you on cholesterol medication? ____ ____

5. Are you on a medically supervised diet? ____ ____

6. Have you ever been diagnosed with an eating disorder? ____ ____

7. Have you ever had a stroke? ____ ____

1. Have you ever been diagnosed with cancer? ______ ______

9. Have you ever had Hepatitis B, C, or HIV? ____ ____

10. Do you have or ever had tuberculosis? ____ ____

11. Are you currently enrolled in any other study? ____ ____

12. Are you planning to move from area in next 30 days? ____ ____

13. Has your doctor told you to limit physical activity? ____ ____

## Females

14. Have you had a baby recently or are you

planning to become pregnant within the next 30 days? ____ ____

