**Exclusion Criteria**

The Study Physician, [name], and Principal Investigator may exclude individuals from the study for any or no reason.

A past history and/or physical examination or laboratory findings of a medical condition including (but not limited to):

- - Cardiovascular, respiratory, gastrointestinal, neuromuscular, neurological, or psychiatric conditions.
  - Musculoskeletal problems interfering with exercise.
  - Immunodeficiency diseases or a positive HIV test.
  - Malignancies in the past 5 years, with the exception of skin cancer therapeutically controlled.
  - Any other medical condition or disease that is life-threatening or that can interfere with or be aggravated by exercise

**Recruitment and consent procedures.** The Institutional Review Board and the Data Safety Monitoring Board will approve all procedures and study protocol at the Pennington Biomedical Research Center. Upon enrollment, each participant will be asked to sign an approved written informed consent form which details the purpose of the study, requirements for participation, and the potential benefits and risks. It will also indicate that participation is voluntary and may be terminated at any time.

**Sources of research material.** The procedures for obtaining research materials will include interviews, and questionnaires. Trained and qualified staff will perform these tasks. Data will be confidentially collected directly from study participants, to be used specifically for research purposes. All information and response to intervention will be documented in each participant’s permanent record with a unique identification number. No identifying information will be released from the study site. All information will be treated as confidential.

**Gender and minorities.** The study population will consist of adults (male and female) of all races, age 40-64 years. Children and adolescents will not be included in this study because the intervention strategy and materials are not

appropriate for this age group.

**Privacy.**  Privacy in the context of this study includes confidentiality of data and personal information. During interviews and measurements, the study staff will ensure full privacy of participants and will ensure that the data are stored in a secured area.

**Right-to-know.** All information obtained from each participant will be available to that participant.

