# FEMALES ONLY

Can you still have children? Yes No

If no, why not? Complete Hysterectomy Partial Hysterectomy

Postmenopausal Tubal Ligation

Other; cause ___________________________________

How did you learn of the study? Flyer Radio TV Newspaper Screening Event / Presentation Word of Mouth

Mailout / Brochure Billboard Email / Website Other: _________________________________

Telephone Screening Status: Eligible ( I) Rejected ; Reason for Reject: Heart Disease Diabetes

High Blood Pressure Cholesterol Medications

Diet Eating Disorder

Stroke Cancer

Medical History Other Study

Moving Limited Physical Activity

Recent Pregnancy Other __________________

Interviewer Initials: _________ Interview Date: _______________________

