###### Note: With the exception of question 3, to qualify all other answers must be NO.

**OVER →**

**Education (check the highest level completed)**

1. Grades 0-8 
2. Some High School 
3. High School diploma/GED 
4. 1-3 years college, business or technical school 
5. College degree 
6. Post graduate degree 

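### No screening form asks about current pregnancy, and Appendix C reaches several listed exclusion categories only through single diagnoses or not at all

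*Protocol*

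**What the plan says.** The section on recruitment and screening gives a screening form the task of separating eligible from ineligible people. The General item under Measurements says that the initial screening form (Appendix B) and the study-specific form (Appendix C) supply the health information, including medical history.

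The Exclusion Criteria open with a discretionary power: the study physician and "Principal Investigator may exclude individuals from the study for any or no reason". They then refer to "A past history and/or physical examination or laboratory findings of a medical condition including (but not limited to", followed by a list that begins with "Cardiovascular, respiratory, gastrointestinal, neuromuscular, neurological, or psychiatric conditions". Pregnancy is not on that list.

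Appendix C has 13 questions for everyone and one for women. Question 14 begins "Have you had a baby recently or are you" and ends "planning to become pregnant within the next 30 days". The note after the questions states: "With the exception of question 3, to qualify all other answers must be NO". Question 3 is the item on high blood pressure.

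Appendix B asks women only whether they can still have children. Its reject reasons include a recent pregnancy (the last two boxes read "Recent Pregnancy Other") but not a current one.

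**The concern.** Question 14 screens for the time before a pregnancy and the time after one, but not for the pregnancy itself. A form that rejects women on either side of that state can hardly be meant to pass those within it, yet its wording does.

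The second part is a mismatch between a list and the form that applies it. The Exclusion Criteria name whole body systems, while Appendix C asks about a handful of diagnoses. Staff who follow the form can enrol someone whom the list, read literally, covers.

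Two things are at stake.

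- **Safety.** The pedometer handout describes adding 60 minutes of moderate activity, about 6,000 steps, as a good guideline. Whether that suits a given participant should be judged on information that was actually collected.
- **Eligibility.** BMI is an inclusion criterion, and weight and waist are measured at baseline and at the end. In a pregnant participant these do not carry their intended meaning. An enrolled participant with a listed condition may also have to be reported as a protocol deviation.

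**Working it through.** The protocol gives no figure to reproduce. The check sets the exclusion list against every health question on the forms shown.

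**Step 1: current pregnancy.**
- Appendix C, question 14: recent birth and planned pregnancy. Both can be answered NO by a woman who is pregnant now.
- Appendix B: ability to have children, and a reject box for recent pregnancy. Neither asks about the present.
- PAR-Q: seven items, none of which mentions pregnancy.
- Direct questions on current pregnancy: 0 on three forms.

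**Step 2: the listed body systems.**

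| Category in Exclusion Criteria | Item in Appendix C | Example that can pass on all-NO answers |
| --- | --- | --- |
| Cardiovascular | Heart disease (1); high blood pressure (3, exempt from the NO rule) | not pursued here |
| Respiratory | Tuberculosis (10) only | asthma |
| Gastrointestinal | No general item; hepatitis B or C (9) is the nearest | bowel disease |
| Neuromuscular | None | any such condition without medical advice to limit activity |
| Neurological | "Have you ever had a stroke" (7) only | epilepsy |
| Psychiatric | Eating disorder (6) only | depression |

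Three systems are thus reached through one diagnosis each, and two have no general item.

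**Step 3: can the other gates close the gap?**
- Question 13 (medical advice to limit activity) and PAR-Q item 6 (any other physical reason not to follow a program) work only if the person has had such advice or sees such a reason.
- PAR-Q item 3 asks about faintness and dizziness, which touches the neurological category by symptom only.
- A yes on the PAR-Q leads to postponement of vigorous exercise and possible medical clearance. The questionnaire does not state exclusion.
- The open medication question in Appendix B may reveal a treated condition but not an untreated one.
- The Medical History and Other reject boxes in Appendix B record a reason once it is known. They do not elicit it.
- Discretionary exclusion can act only on what has been disclosed.
- Examination and laboratory findings are named as sources, but neither appears among the measurements or as a row in the Study Measurement Schedule.

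**Step 4: size, on assumed inputs.** The protocol gives no prevalences, so all of these are assumptions.
- Pregnancy: if 15 of the 60 participants are women from 35 to the mid-40s and 1% to 3% are pregnant, the expected number is 15 × 0.01 = 0.15 to 15 × 0.03 = 0.45.
- Body systems: if 10% to 15% of participants have a respiratory, neurological or psychiatric condition that Appendix C does not ask about, the number is 60 × 0.10 = 6 to 60 × 0.15 = 9. This is an upper figure, because it supposes that no other gate catches anyone.

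**The case against.** Four stronger readings are tempting, and the protocol does not support them.

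- **A reader might infer that the form never asks about these systems.** It does, narrowly: tuberculosis, stroke and eating disorder each belong to a listed category.
- **A reader might infer that all-NO answers are enough to enrol.** The note states a necessary condition. Appendix B, the PAR-Q and the judgment of the study physician and Principal Investigator come on top. The inclusion criteria also require physical capability and an understanding of the exclusion criteria, so participants may volunteer a listed condition.
- **A reader might infer that the protocol excludes pregnant women and then contradicts itself.** It states no such exclusion. The intent is inferred from question 14 and one reject box. The inference is strong, but it remains an inference. Consent pages were also removed from the text at hand and may mention pregnancy.
- **A reader might infer that an examination is promised and then omitted.** The wording joins history, examination and laboratory findings with and/or, so history alone can suffice.

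It can also be argued that the list is not meant to exclude every gastrointestinal or psychiatric condition. It follows a discretionary sentence, closes with conditions that interact with exercise, and sits under a stated aim of keeping as many people eligible as possible. That is a fair reading, but it supports reconciling the two texts, because the list as written carries no such limit for these systems.

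Finally, the effect on results is slight. Weight and waist enter none of the hypotheses. Screening precedes randomization, so any misclassified participants fall in both groups alike in expectation. That stands and limits the weight of the point, but it does not remove the safety and eligibility gap.

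**Conclusion.** The point holds in this form: on the forms shown, nobody is asked about current pregnancy, and Appendix C is narrower than the Exclusion Criteria for the respiratory, gastrointestinal, neuromuscular, neurological and psychiatric categories. People in those situations can pass Appendix C with truthful NO answers, and the remaining gates depend on chance disclosure.

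The size is modest. Fewer than one pregnant participant is expected under the assumptions used. The count for the body systems depends both on an assumed prevalence and on how literally the list is read. The pregnancy part rests on the inferred intent of question 14. Neither part threatens the analysis of the hypotheses. The correction is worth making because it is nearly free and concerns participant safety and consistent eligibility decisions.

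**What to change.** 1. Reword question 14 so that it asks about current pregnancy as well as recent birth and planned pregnancy. State the resulting rule in the Exclusion Criteria, so that the form applies a written criterion.
2. Make the Exclusion Criteria and Appendix C name the same conditions. Either add an item to the form for each listed system, or narrow the list to the conditions that the form asks about. Match the reject reasons in Appendix B to the result.
3. Leave to the study physician which conditions exclude. This review takes no position on that.

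The cost is an edit to the two forms and one protocol list, with no added test or visit. The downside is a slightly longer screening call if items are added, and possibly a few more exclusions in a study that seeks 60 participants from one parish.

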###### Note: With the exception of question 3, to qualify all other answers must be NO.

**OVER →**

**Education (check the highest level completed)**

1. Grades 0-8 
2. Some High School 
3. High School diploma/GED 
4. 1-3 years college, business or technical school 
5. College degree 
6. Post graduate degree 

**What is your present employment status?**

1. Employed full time (at least 36.5 hrs/week) 
2. Employed part-time (at least 20hrs/week) 
3. Retired 
4. Unemployed 

5. Medical disability 

**What is your approximate household income?**

1. Less than $10,000 per year 
2. $10,000 - $19,999 per year 
3. $20,000 - $29,999 per year 
4. $30,000 - $49,999 per year 
5. $50,000 - $69,999 per year 
6. $70,000 - $89,999 per year 
7. $90,000 - $109,999 per year 
8. $110,000 - $139,999 per year 
9. $140,000 per year and above 

**What is the total number of people living in your household?**

1. 1 

2. 2 

3. 3 

4. 4 

5. 5 

6. 6 

7. 7 or more 

###### Appendix D

###### AMPM

###### 24-Hour Recall

[figure not shown]

**What is AMPM?**

- Computerized method for collecting interviewer-administered 24-hour dietary recalls either in person or by telephone.
- Research-based, multiple-pass approach employing 5 steps designed to enhance complete and accurate food recall and reduce respondent burden.
- Method used in ***What We Eat in America***, the dietary interview component of the National Health and Nutrition Examination Survey, and other research studies.

**Features of AMPM**

- Employs research-based strategies to enhance dietary recall:
      - Respondent-driven approach allowing initial recall to be self-defined
      - Association with the day's events
      - Probes for frequently forgotten foods
      - Repetition with minimal burden
      - Reviews 24-hour day
      - Placement of foods with eating occasions
- Interviewer-administered, in person or by telephone
- Extensive automated capabilities, including:
      - Unique questions and response options specific for each food
      - Routing of questions based on previous responses
      - Food lookup tables reflecting today's food market
      - Ability to add, change, or delete foods anytime during the interview
      - Automated edit checks performed during data entry
      - Notepad features for interviewer comments
- Companion Food Model Booklet, an aid for estimating portion sizes
- Companion, supportive computer systems for auto-coding, manual coding, and quality control
- Utilizes the Food and Nutrient Database for Dietary Studies

| **5-Step Multiple-Pass Approach** | | |
| --- | --- | --- |
| **Step** |  | **Purpose** |
| **Quick List** |  | Collect a list of foods and beverages consumed the previous day. |
| [figure not shown] |  |  |
| **Forgotten Foods** |  | Probe for foods forgotten during the Quick List. |
| [figure not shown] |  |  |
| **Time &  Occasion** |  | Collect time and eating occasion for each food. |
| [figure not shown] |  |  |
| **Detail Cycle** |  | For each food, collect detailed description, amount, and additions. Review 24-hour day. |
| [figure not shown] |  |  |
| **Final Probe** |  | Final probe for anything else consumed. |

Read more about USDA's Automated Multiple-Pass Method:

Bliss, R.M. (2004). [Researchers produce innovation in dietary recall.](http://hdl.handle.net/10113/23049)*Agric Res 52*(6):10-12.

McBride J. (2001). [Was it a slab, a slice, or a sliver? High tech innovations take survey to new level.](http://hdl.handle.net/10113/23006)*Agric Res 49*(3):4-7.

**Information Collected by AMPM**

The AMPM collects a list of all foods and beverages consumed in a 24-hour period. Information captured by AMPM includes:

- For each food... 
      - Description of food
      - Additions to the food (for example, milk on cereal or cream in coffee)
      - Combination code that identifies foods eaten together
        (such as milk added to cereal)
      - Amount of food consumed
      - Time eaten
      - Name of eating occasion
      - Where obtained
      - Eaten at home or not
- Water consumption – bottled and tap water
- Use of salt in preparing foods and at the table
- Whether the amount of food consumed on the recall day was much more than usual, usual, or much less than usual
- Currently on a diet to lose weight or some other health-related reason

**AMPM Applications**

The AMPM is being used in large national surveys in the United States and Canada:

- [***What We Eat in America***, NHANES](http://www.ars.usda.gov/Services/docs.htm?docid=13793) – Yearly since 2002: two recalls each for 5,000 individuals.
- Canadian Community Health Survey, 2004 – 30,000 recalls.
- Other studies in the United States.

###### Appendix E

Physical Activity Readiness Questionnaire (PAR-Q)

**
[figure not shown]
**

**Physical Activity Readiness Questionnaire (PAR-Q)**

For most people, physical activity should not pose any problems or hazard. PAR-Q has been designed to identify the small number of adults for whom physical activity might be inappropriate or those who should have medical advice concerning the type of activity most suitable.

| 1. | Has your doctor ever said you have heart trouble? | Yes | No |
| --- | --- | --- | --- |
| 2. | Do you frequently suffer from pains in your chest? | Yes | No |
| 3. | Do you often feel faint or have spells of severe dizziness? | Yes | No |
| 4. | Has a doctor ever said your blood pressure was too high? | Yes | No |
| 5. | Has a doctor ever told you that you have a bone or joint problem such as arthritis that has been aggravated by exercise, or might be made worse with exercise? | Yes | No |
| 6. | Is there a good physical reason not mentioned here why you should not follow an activity program even if you wanted to? | Yes | No |
| 7. | Are you over age 65 and not accustomed to vigorous exercise? | Yes | No |

**If a person answers yes to any question, vigorous exercise or exercise testing should be postponed. Medical clearance may be necessary.**

Signature Date

Witness Date

[name] Date

###### Appendix F

###### Physical Activity

###### Educational Materials

# Get Moving!

**This educational piece is designed to help you learn:**

[figure not shown]
 Benefits to exercising

[figure not shown]
 How to get started with an exercise regime

[figure not shown]
 How to prevent sore muscles or cramps

[figure not shown]
 How to properly stretch

[figure not shown]
 When to stop exercising

[figure not shown]
 Understand the F.I.T.T. principle

**Research shows that being more active will:**

[figure not shown]
 Help you lose weight and keep it off.

[figure not shown]
 Help you feel better.

[figure not shown]
 Make you more physically fit.

[figure not shown]
 Make it easier for you to do your daily work, like climbing stairs.

[figure not shown]
 Lower your risk for some kinds of cancer.

[figure not shown]
 Lower your risk for heart disease.

Being active:

- Raises HDL cholesterol (the “good” cholesterol in the blood).
- Lowers triglycerides.
- Lowers blood pressure.

**What are the recommendations?**

**For the first time, the USDA Dietary Guidelines for Americans spell out how much physical activity you need. They recommend:**

- **At least 30 minutes of moderate-intensity physical activity, above your usual activity, on most days of the week to reduce the risk of chronic disease in adulthood. Greater health benefits, say the Guidelines, can be reaped with a more intense program or one that is of longer duration.**
- **About 60 minutes of moderate- to vigorous-intensity activity most days of the week to help manage body weight and prevent gradual, unhealthy body-weight gain in adulthood.**
- **At least 60 to 90 minutes of moderate-intensity physical activity daily to sustain weight loss in adulthood.**

Not all ways of being active will strengthen your heart, only those that are “F.I.T.T.”

**F.I.T.T. stands for Frequency, Intensity, Time, and**

**Type of Activity**

|  | **What to do:** |
| --- | --- |
| **Frequency**  (How often you are active) | - Try to be active on **most days of the week**. - Increase slowly. |
| **Intensity**  (How hard you are working while being active: how fast your heart beats) | - Work hard but not too hard. Keep your intensity **similar to a brisk walk.** - Breathe fast enough that you **can talk but not sing.**   If you can break into song, speed it up!  If you have trouble breathing and talking, slow down. |
| **Time**  (How long you are active) | - Stay active for **at least 10 minutes in a row without breaks**. - The total minutes of activity you do per week should be your **activity goal for the week or more.** |
| **Type of activity** | - Do heart fitness activities--those that make your heart work, such as brisk walking, riding your bike, others. - Use large muscle groups (such as legs and arms). - Last 10 minutes or longer. |

**Finding the time**

Many people say, “I would be more active if I could find the time.”

**You *can* find the time to be active.** Here’s how:

- Set aside **one block of time on at least 3 days a week** to be active. Do something you like. For example, get up early and walk the dog before work.
- Look for **short periods of free time (at least 10 minutes)** during the day. Use the time to be active. For example, walk during your coffee break, for part of your lunch hour, and/or between meetings at work.
- Park further away from the store or where you work.

**Make a written plan for every day of the week.** Plan what activity you will do. Plan when and for how long you will do it.

Here’s an example of small activity bouts:

| **Day** | **What I will do** | **When** | **Minutes** |
| --- | --- | --- | --- |
| **Monday** | Walk the dog | 7:00 am | 10 |
| **Tuesday** | Walk during coffee break | 10:00 am | 10 |
| **Wednesday** | Ride a bike | 7:00 am | 10 |
| **Thursday** | Walk during coffee break | 10:00 am | 10 |
| **Friday** | Walk the dog | 7:00 am | 10 |
| **Saturday** |  |  |  |
| **Sunday** |  |  |  |
| **Total minutes for the week:** | | |  |

Aim for the recommended minutes of physical activity per day and record your total for the week. Recording helps you stay on track. Several short activity sessions per day can add up to big benefits!!

